## Abstract

**Background:** Major Depressive Disorder (MDD) affects more than 264 million people worldwide. Current treatments include the use of psychotherapy and/or drugs, however ~30% of patients either do not respond to these treatments, or do not tolerate the side effects associated to the use of pharmacological interventions. Thus, it is important to study non-pharmacological interventions targeting mechanisms not directly involved with the regulation of neurotransmitters. Several studies demonstrated that transcranial Direct Current Stimulation (tDCS) can be effective for symptoms relief in MDD. However, tDCS seems to have a better effect when used as an add-on treatment to other interventions.

**Methods/Design:** This is a study protocol for a parallel, randomized, triple-blind, sham-controlled clinical trial in which a total of 90 drug-naïve, first-episode MDD patients (45 per arm) will be randomized to one of two groups to receive a 6-weeks of CBT combined with either active or sham tDCS to the dorsolateral prefrontal cortex (DLPFC). The primary outcome will depressive symptoms improvement as assessed by the Montgomery-Asberg Depression Rating Scale (MADRS) at 6-weeks. The secondary aim is to test whether CBT combined with tDCS can engage the proposed mechanistic target of restoring the prefrontal imbalance and connectivity through the bilateral modulation of the DLPFC, as assessed by changes over resting-state and emotional task eliciting EEG.

**Discussion:** This study evaluates the synergetic clinical effects of CBT and tDCS in the first episode, drug-naïve, patients with MDD. First episode MDD patients provide an interesting opportunity, as their brains were not changed by the pharmacological treatments, by the time course, or by the recurrence of MDD episodes (and other comorbidities).

**Trial Registration:** This study is registered with the United States National Library of Medicine Clinical Trials Registry (NCT03548545). Registered June 7, 2018, clinicaltrials.gov/ct2/show/NCT03548545. Protocol Version 1.

## Background

Major Depressive Disorder(MDD) is widely recognized as a staggering global healthcare challenge, as well as a potentially lethal illness (1). The worldwide prevalence of Depression is about 3.4% [2–6%], and mild forms of depression are the most prevalent−13%, as compared to 4% for moderate forms and 5.1 % for severe forms of depression (2). The prevalence in females is about 4.1% and about 2.7% in males (2). Overall, MDD is thought to affect 264 million people worldwide, thus ranking second in the most common causes of disability with prospects of becoming the first by 2040 (3).

The current standard care for MDD involves the use of psychotherapy, antidepressant medication, or a combination of both. Despite the costs involved in these interventions, the efficacy of such treatments may have been overestimated, with recent data suggesting that remission rates can be as low as 23% depending on the self-report scale used (4). Furthermore, 30% of patients suffering from MDD still exhibit depressive symptoms despite the appropriate psychological and pharmacological treatments (5). In order to overcome this, several treatments are frequently combined, usually by the use of drug augmentation and/or combination of different drugs, which often increases the risk of adverse effects (6). Thus, the development of effective treatment alternatives for MDD, which includes non-pharmacological interventions targeting mechanisms not directly involved with the regulation of neurotransmitters, is an urgent research priority. However, in order to do so, it is important to understand the underlying neural mechanisms involved in MDD.

Evidence coming from several electroencephalography (EEG) (7–9), neuroimaging (10, 11), and neuromodulation (12–15) studies showed that the dorsolateral prefrontal cortex (DLPFC) is as an important area of dysfunction in depression, mainly due its left hypo and right hyper-functioning. This inter-hemispheric imbalance over the DLPFC has been shown to be an indicator of lifetime MDD, or in conjunction with depressive self-schema (i.e., an interconnected negative internal representation of the self that has been associated to the onset and maintenance of depressive state (16, 17) to be a predictor of a first prospective MDD episode (18). Nevertheless, some studies failed to show the link between decreased left frontal activation and depression (19).

Transcranial direct current stimulation (tDCS) is a non-invasive method of brain stimulation that is capable of depolarizing or hyperpolarizing the neural membrane and as such, it has been used in people suffering from depression, by placing the anode (excitatory) over the left and the cathode (inhibitory) over the right DLPFC, or by placing the anode over the left DLPFC and the cathode over the right supra-orbital region.

For instance, in one study, 64 MDD patients were randomized to 15 sessions of 2 mA tDCS over 3 weeks, and tDCS was shown to be able to decreased MDD symptoms (20). However, in another study, not only active tDCS was superior to sham but also the combination of tDCS with sertraline was significantly more effective in reducing depressive symptoms than either treatment alone (21). Although tDCS *per se* showed promising results in treating MDD, the previous trial highlights that the effects of tDCS can be enhanced by combining it with other interventions. Overall, tDCS seems to decrease MDD symptoms by a pooled effect size of 0.36 (22). Moreover, according to a recent individual patient data meta-analysis, tDCS seems to be less effective in high-resistant patients, suggesting that tDCS may be a promising add-on therapy to therapies such as the cognitive behavioral therapy (CBT) (23) or cognitive control therapy (24, 25).

CBT is an empirically validated therapy for the treatment of MDD. Several studies have demonstrated the efficacy of CTB alone (26, 27) or as adjuvant to medication (28–30) in acute depression. Another advantage of CBT over anti-depressant drugs is its long-term effects, namely protecting against relapses and recurrences after active treatments has ended (27, 31, 32). Additionally, CBT is a well-established therapy that can restore or normalize abnormal brain activity, namely prefrontal alpha activity (33). Namely, an increase in left frontal brain activity after CBT in individuals with anxiety and depression.

It is important to highlight that MDD seems to induce profound changes in the brain, namely structural alterations in fronto-cingulate-striatal circuits (34–36). However, and somewhat surprisingly, first episode MDD patients have not been extensively studied with tDCS (37, 38). These first episode MDD patients provide an interesting opportunity, as their brains were not changed by the pharmacological treatments, by the time course, or by the recurrence of MDD episodes (and other comorbidities).

## Purpose, Primary and Secondary Outcomes

Therefore, we propose to study the clinical and mechanistic effects of the combination of two well-studied interventions—CBT and tDCS—for the treatment of MDD in drug naïve first episode patients. The primary outcome will be the clinical effects (severity of depression/mood amelioration), as measured by the Montgomery-Asberg Depression Rating Scale (MADRS). Secondary outcomes will be resting state and emotional task eliciting EEG, which will be useful simultaneously to understand the neural effects of the intervention, as well as potential response predictors for future trials.

## Research Question, Aims, Hypothesis

By combining two interventions that showed promising results in MDD (CBT and tDCS), we aim to investigate the clinical and underlying neurophysiological effects in first-episode drug naïve MDD patients. The main research question underlying this proposal is whether tDCS as add-on therapy to CBT in drug naïve, first-episode MDD patients could produce greater significant clinical improvements, as measured by the MADRS, when compared to CBT alone. We hypothesize that the combination of these therapies will produce a synergetic effect in the brain, potentiating the effects of CBT and decreasing the depressive symptomatology as assessed by the MADRS.

A secondary aim will be to perform the dose calculation (number of sessions) required to induce a clinically significant effect (50% decrease in the MADRS score). The underlying hypothesis is that the combination of tDCS with CBT will require a lesser number of sessions in order to elicit this clinical meaningful effect.

The second major scientific question is whether these clinical improvements will be correlated with the rebalancing of the inter-hemispheric asymmetry of EEG alpha activity toward the left hemisphere, as assessed by resting-state and emotional task eliciting-EEG. Here, the hypothesis is that both interventions (combined and alone) will reduce the inter-hemispheric alpha imbalance, as indexed by EEG power; however, that reduction will be more pronounced in the group that received the add-on intervention, as compared to CBT alone.

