**Figure 1 F1:**
[figure not shown]
Overview of the Study design (tDCS, transcranial Direct Current Stimulation; CBT, Cognitive Behavioral Therapy).

Patients will complete a 6-weeks treatment that involves 18 tDCS sessions (active or sham) and 12 CBT sessions. For the first 2 weeks of intervention, they will receive 10 daily sessions of tDCS (from Monday to Friday) and 4 sessions of CBT (combined at same time with tDCS for the first 30 min, on Monday and on Friday). They will then receive two booster sessions of tDCS combined with CBT will be on weeks 3, 4, 5, and 6 (Figure 2B).

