**PRIMARY AND SECONDARY OUTCOME ASSESSMENTS**											
The satisfaction with life scale (SWL)		X			X			X		X	
The pittsburgh sleep quality index (PSQI)		X			X			X		X	
State-trait anxiety inventory (STAI-Y)		X			X			X		X	
Beck anxiety inventory (BAI)		X			X			X		X	
Beck's depression inventory (BDI)		X			X			X		X	
Montgomery-asberg depression rating scale (MADRS)		X			X			X		X	
Blinding questionnaire								X			
Visual analog scales (VAS)—pre and post				X			X				

Structured CBT sessions will follow the NICE guidelines from the National Institute for Health and Care Excellence (39). Patients will receive a total of 12 CBT sessions administered biweekly for 6 weeks. Mood, will be evaluated at the end of each week, as to perform the dose calculation (i.e., number of sessions) required to induce a clinical significant effect of at least 50% decrease in the MADRS scores.

In addition to the primary outcome measure (MADRS), secondary outcome measures will be clinical response as measured by scores on the 17-item Hamilton Depression Rating Scale, Beck Depression Inventory (BDI), Beck Anxiety Inventory (BAI), clinician-rated Clinical Global Impression–Severity of Illness scale, and quality of life (QoL). These scales will be used at baseline, week 2, 4, 6, and follow-ups (up to 6-month follow up).

Resting-state EGG assessments will be performed on baseline session, on weeks 2 and 6. These assessments will allow us to assess the neural effects of these interventions in the brain.

The Standard Protocol Items: recommendations for Interventional Trials (SPIRIT) statement were used as a framework for developing the study methodology for this trial (40, 41).

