These changes in EEG patterns have been used to direct several interventions, such as tDCS or TMS, however most study lack in the assessment of the real changes in EEG activity. For instance, based on this neurobiological basis, the main target for treating depressive symptoms using non-invasive brain stimulation (NIBS) techniques, such as tDCS and TMS, have been both the left (hypoactive) and right (hyperactive) DLPFC, by placing anodal (excitatory) over the left and cathodal (inhibitory) over the right DLPFC (76, 77). Using this mechanistic approach of facilitating the activation of the left DLPFC relative to the right, beneficial emotional, and cognitive effects in MDD were shown emotional and cognitive effects in MDD (18, 78, 79). Moreover, we chose to include adults with first episode of MDD only as to increase homogeneity of our study sample and thus increase internal validity of our findings. There are several advantages of studying the combination of these treatments in first episode MD drug-naive patients, as their brains were not changed by the pharmacological treatments, by the time course of the condition, or by the recurrence of MDD episodes (and other comorbidities). Second, combining tDCS and CBT are two therapies that have been shown to improve MDD. Moreover, tDCS is a safe, of easy administration, and not expensive non-invasive brain stimulation technique that has been shown to be effective in neuromodulating our target mechanism (imbalance over the DLPFC). Also, CBT is the golden standard treatment for MDD and has also shown to be able to neuromodulate brain structures involved in MDD. Thus, if we show that tDCS combined with CBT produce greater significant clinical improvements in MDD, this may reduce the global burden of MDD (for instance, by reducing the number of therapy sessions and the number of relapses and by producing larger long-term effects).

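### Both arms are scheduled for the same fixed course, so the trial can show whether response comes earlier with active tDCS but not how many sessions are required

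*Protocol article*

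**What the plan says.** The section Research Question, Aims, Hypothesis gives a secondary aim to "perform the dose calculation (number of sessions) required to induce a clinically significant effect", set at a 50% decrease in MADRS, and continues: "The underlying hypothesis is that the combination of tDCS with CBT will require a lesser number of sessions". The text after Table 1 repeats the aim and says where the figure will come from: "Mood, will be evaluated at the end of each week, as to perform the dose calculation". The Discussion expects the active arm to need fewer sessions to reach the clinical outcome. It later suggests that the combination may lower the burden of depression, for instance "by reducing the number of therapy sessions and the number of relapses and by producing larger long-term effects".

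The course itself is set out under Trial Design, Setting and Registration, after Figure 1: "Patients will complete a 6-weeks treatment that involves 18 tDCS sessions (active or sham) and 12 CBT sessions". In the first two weeks "they will receive 10 daily sessions of tDCS (from Monday to Friday) and 4 sessions of CBT", and then "two booster sessions of tDCS combined with CBT will be on weeks 3, 4, 5, and 6". The text after Table 1 agrees on CBT: "Patients will receive a total of 12 CBT sessions administered biweekly for 6 weeks".

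The Randomization section allocates patients 1:1 to two groups, which differ only in active or sham stimulation. The text after Figure 2 lets a patient miss one or two sessions and make them up in the following week. The article describes no arm, step or stopping rule that varies the number of sessions.

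**The concern.** A required dose is a statement about what would happen if treatment stopped at a given number of sessions. To estimate it, patients must differ in the number they receive for reasons unrelated to their prognosis. Here a patient who first reaches a 50% decrease after 10 tDCS sessions is still scheduled for the other 8, and no comparable patient is allocated to stop at 10.

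A trial in which the number of sessions had no effect at all would still produce a required number. It would be the count scheduled by the week in which patients happened to improve. At stake is a secondary conclusion that says more than the design can support. The aim also leaves open which session is being counted, tDCS or CBT, and the two counts give different answers from the same patients.

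**Working it through.** **Inputs.** The text after Figure 1 gives 10 tDCS sessions (Monday to Friday) and 4 CBT sessions (Monday and Friday) in weeks 1-2, then two combined sessions a week in weeks 3-6.

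**1. The plan's own totals.** tDCS: 10 + 4 × 2 = 18. CBT: 4 + 4 × 2 = 12. Both match the stated course. The article gives no numerical target for the dose aim.

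**2. Cumulative sessions, the same in both arms.**

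| End of week | 1 | 2 | 3 | 4 | 5 | 6 |
|---|---|---|---|---|---|---|
| tDCS | 5 | 10 | 12 | 14 | 16 | 18 |
| CBT | 2 | 4 | 6 | 8 | 10 | 12 |

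**3. Can sessions be separated from time?** CBT count = 2 × week. tDCS count = 5 × week in weeks 1-2, and 10 + 2 × (week − 2) in weeks 3-6. Each is an exact function of week. A design matrix with six week indicators plus the two counts has 8 columns but rank 6. No session effect is estimable beyond elapsed time, and the two counts cannot be told apart.

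**4. What this means for a required number.** Assume, for illustration only, weekly response probabilities among patients not yet responding of 5, 10, 12, 12, 12 and 12%. Cumulative response at week 6 is 1 − 0.95 × 0.90 × 0.88⁴ = 49%. Two explanations fit this equally well:
- Responses after week 2 need the later sessions. Stopping at 10 tDCS sessions would then give 1 − 0.95 × 0.90 = 14.5% at week 6.
- Responses after week 2 are delayed effects of the first 10 sessions, or natural recovery. Stopping at 10 would then still give 49%.

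The observed data are identical in both cases, so the trial cannot choose between them.

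**5. The unit (illustration, weekly MADRS assumed).** Response at week 2 instead of week 3 saves 1 − 10/12 = 17% of tDCS sessions but 1 − 4/6 = 33% of CBT sessions. One patient's one-week gain thus gives two different results.

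**6. Is MADRS rated often enough?** The article gives three accounts of on-treatment assessment:
- End of each week for mood, for the dose calculation (text after Table 1).
- Weeks 2, 4 and 6 for the clinical scales (same text).
- 15 days and post-intervention only for MADRS (Table 1).

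On Table 1, response during treatment can be placed only at about 10 or 18 tDCS sessions, and the contrast in step 5 could not be observed.

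**7. The other schedule.** The text after Figure 2 gives 6 CBT sessions in the first two weeks (3 a week), and boosters by weeks 4 and 6. CBT would then stand at 3 and 6 after weeks 1 and 2, so the CBT row in step 2 and the 33% in step 5 would not follow. That schedule too is fixed and common to both arms, so step 3's conclusion that sessions cannot be separated from time is unchanged.

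**The case against.** The strongest reply is that the hypothesis attached to the aim is a comparison between arms, and that comparison is sound. With one schedule for both arms, cumulative sessions rise strictly with week, so a rank-based test such as log-rank gives the same answer in weeks or in sessions. The sham arm controls for natural recovery and time in CBT. This stands. A reader might infer that nothing about the speed of response can be learned, and the design does not support that reading.

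A reader might also infer that the authors plan to recommend shorter treatment. The article does not say so. The Discussion sentence on reducing sessions is conditional and hedged, and no shorter course is proposed. The aim, the text after Table 1 and the Discussion's expectation of fewer sessions do, however, state the session claim without a hedge.

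It would be too strong to say that every patient follows exactly one calendar, because one or two sessions may be missed. Those departures are small, patient-driven and can be made up, so they cannot identify a dose. The percentages in the working depend on one of two conflicting schedules and on weekly MADRS, so they illustrate the problem and do not measure its size in this trial.

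Finally, the full protocol or analysis plan may define the analysis. That could settle the method, but it could not supply variation in session number that the design lacks.

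**Conclusion.** The concern holds in a limited form. The number of sessions required within an arm is not identified, because scheduled session count and elapsed week carry the same information and tDCS and CBT counts move together. The randomised contrast identifies whether the 50% decrease comes earlier with active than with sham tDCS under the full 6-week course.

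This conclusion rests on the fixed common course and holds under either description of the schedule. The 17% against 33% difference holds only on the schedule after Figure 1 with weekly MADRS. The 49% and 14.5% rest on assumed weekly probabilities. The point affects a secondary aim and its interpretation. The primary comparison and the sample size are not affected.

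**What to change.** - In Research Question, Aims, Hypothesis, in the text after Table 1 and in the Discussion, replace the dose calculation with time in weeks to first 50% MADRS decrease, compared between arms as randomised.
- Use a method suited to discrete assessment times (interval-censored or discrete-time), with patients who have not responded censored at their last on-treatment assessment.
- Limit the conclusion to earlier response under the fixed 6-week course. Do not present the trial as showing how many sessions are required or that sessions can be reduced, and word the hedged Discussion sentence to match.
- Reconcile the end-of-week ratings with Table 1 and with the weeks 2, 4 and 6 statement, and say whether the weekly rating is the MADRS.
- Reconcile the two schedules: 4 or 6 CBT sessions in weeks 1-2, and boosters in weeks 3-6 or by weeks 4 and 6.

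The cost is the wording of a secondary aim and a less ambitious claim. If weekly MADRS is already planned, no visits are added. If Table 1 is the operative schedule, there are only two on-treatment assessment times. The comparison would then be correspondingly coarse unless weekly ratings are added.

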## Methods

### Trial Design, Setting and Registration

This is a parallel, randomized, triple-blind, sham controlled clinical protocol in which a total of 90 drug-naïve, first-episode MDD outpatients (45 per arm) will be randomized to one of two groups: active bilateral tDCS over the DLPFC combined with CBT or sham tDCS combined with CBT (Figure 1).

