### Sample Size Calculation

For the sample size calculation, we assume an effect size(d) of 0.66 [upper limit for the 95% CI of the pooled effect size of tDCS on MDD (22) that for a two-side α of 0.05 and a power of 80%, requires a total of 76 patients (38 per group). We increased the sample size by 15% to 45 per group to account for unexpected factors. This sample size will be adequate to detect this magnitude of effect.

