### Randomization

Once eligibility and consent have been approved and obtained, randomization will occur using the randomized list generated by an automatic web-based randomization program. Patients will be randomly assigned to one of the two groups in a 1:1 allocation ratio. Randomization order will be kept in sealed envelopes; therefore, patients will get their assignment according to the order of entrance in the study. This will also ensure that all patients and all other investigators are kept blind to this assignment for the duration of the study (allocation concealment) (see Figure 1, for study overview).

The randomization procedures described above will be followed for assignment to treatment groups. Following initial screening, during participant enrollment, a research associate will assign them to their randomly generated treatment group, keeping all patients and all other investigators blind to this assignment for the duration of the study.

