We also propose to study, as secondary aim, whether CBT combined with tDCS can engage the proposed mechanistic target, of restoring the prefrontal imbalance and connectivity, by changes over resting-state and task-eliciting EEG. This trial will help to evaluate the efficacy of this combined treatment as compared to CBT alone and to evaluate bilateral alpha activity over the prefrontal cortex. Thus, we also expect to demonstrate that these interventions are able to reduce the inter-hemispheric asymmetry of alpha EEG activity toward the left hemisphere reported in patients with depression. We expect that the combined intervention will induce greater asymmetry reduction (at least 50% minimum reduction). We also expect that this inter-hemispheric imbalance reduction will be correlated with mood improvement.

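### The EEG hypothesis credits both interventions with reducing alpha asymmetry, but with CBT and device sessions in both arms only the added effect of active over sham tDCS is identified

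*Protocol article*

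**What the plan says.** The EEG hypothesis in the protocol article (Research Question, Aims, Hypothesis) has two parts. The first is that "both interventions (combined and alone) will reduce the inter-hemispheric alpha imbalance, as indexed by EEG power". The second is that "that reduction will be more pronounced in the group that received the add-on intervention, as compared to CBT alone".

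The Discussion restates the first part as an intended conclusion: "we also expect to demonstrate that these interventions are able to reduce the inter-hemispheric asymmetry of alpha EEG activity toward the left hemisphere".

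The design section gives two arms: "active bilateral tDCS over the DLPFC combined with CBT or sham tDCS combined with CBT". The text under Figure 1 schedules 18 tDCS sessions (active or sham) and 12 CBT sessions for all patients. No untreated, wait-list, attention-control or healthy retest group is described anywhere.

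On timing, the text after Table 1 states: "Resting-state EGG assessments will be performed on baseline session, on weeks 2 and 6". The Secondary Outcomes section instead gives the end of each treatment week. The point below is the same under either schedule.

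The statistical section for the primary outcome makes a correlation analysis with long-term clinical effects conditional on the imbalance hypothesis being confirmed. It does not say which of the two parts must be confirmed.

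**The concern.** The first part of the hypothesis is a before-after statement about each arm, and the Discussion gives it causal force: the interventions themselves are said to be capable of lowering the asymmetry. That covers CBT as well as the addition of tDCS.

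Patients enter while symptomatic and are recorded again during and after treatment. Natural course, repeat recording and non-specific contact could each move the measure over time. In the arm that the article calls CBT alone, any response to the sham device is added. With no group that has time and retesting but no treatment, these sources cannot be separated from an effect of CBT.

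At stake is the mechanistic conclusion. A fall in the sham arm could be read as CBT normalising prefrontal activity, and a fall in the active arm as the combination doing so. The same fall could also count as confirmation and open the correlation analysis, although it carries no randomised evidence.

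**Working it through.** **1. What randomisation identifies.** Write the mean change in asymmetry in each arm as a sum, where D is drift and retest, S is non-specific and sham response, C is the effect of CBT, and T is the effect of active rather than sham tDCS when given with CBT:

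- sham arm: D + S + C
- active arm: D + S + C + T
- difference, active minus sham: T

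There are two observed means and four unknowns. Only T can be recovered. C cannot be separated from D + S, and neither can C + T. Assignment is randomised ("Patients will be randomly assigned to one of the two groups in a 1:1 allocation ratio"), so D, S and C are shared in expectation and cancel in the difference. The second part of the hypothesis concerns T. The first part concerns C and C + T.

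**2. The plan's own sample size figure.** The Sample Size Calculation section states "we assume an effect size(d) of 0.66", with two-sided 5% and 80% power. The normal approximation gives n = 2(1.960 + 0.842)² / 0.66² = 36.0, so 37 per arm. The noncentral t gives power of 79.98% at 37 and 81.0% at 38, so the stated 38 per group reproduces. Then 38 / (1 − 0.15) = 44.7, so 45. This calculation is for the between-arm clinical contrast. The article gives no figure for a within-arm EEG change.

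**3. Illustration of the within-arm claim.** Inputs:

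- n = 45 per arm (from the article); 38 as a variant with losses.
- Two-sided 5% pre-post t-test in each arm. This is an assumption, because the article specifies no such test.
- No treatment effect, and a time-only shift g in the direction of a fall, in SDs of the change score. This is also an assumption, because the documents give no value.

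The chance of a significant fall in one arm is p = P(T′ > t₀.₉₇₅,ₙ₋₁), where T′ is noncentral t with n − 1 degrees of freedom and noncentrality g√n. The arms are independent, so the chance in both is p².

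| g (SD of change) | one arm, n = 45 | both arms, n = 45 | one arm, n = 38 | both arms, n = 38 |
|---|---|---|---|---|
| 0 | 2.5% | 0.1% | 2.5% | 0.1% |
| 0.1 | 10% | 1% | 9% | 1% |
| 0.2 | 26% | 7% | 22% | 5% |
| 0.3 | 50% | 25% | 44% | 19% |
| 0.4 | 75% | 56% | 67% | 45% |

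For example, at g = 0.3 and n = 45, p = 0.503 and p² = 0.253.

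The both-arms columns match the hypothesis, which is about both interventions. The between-arm test stays at 5% in every row, because g is common to both arms. The within-arm probabilities rise with n, so a larger trial would not cure the problem.

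**The case against.** The strongest reply is that no within-arm test is planned. The only inferential model given is a mixed ANOVA for MADRS with intervention as the between-subject factor, the EEG Analysis section covers signal processing, and the EEG inference may sit in an analysis plan that is not shown. EEG is a secondary outcome. The disputed clause is followed at once by the comparative one, and the Discussion also frames the trial as a comparison with CBT alone. All of this stands. It limits the weight of the point and makes the table an illustration, not an error rate of the plan. It does not remove the point, because the fault is in the stated hypothesis and intended conclusion, and no analysis of these two arms can supply the missing comparison.

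A second reply is that drift may be small. The Discussion describes the asymmetry as also present in people who were depressed in the past, so recovery of mood need not move it. Eligibility does not depend on asymmetry, so there is no selection on this outcome to cause regression to the mean. This too stands as a reason to include small shifts such as 0.1 SD. Retest and contact effects remain possible, and the identification argument does not depend on their size.

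A third reply is that the Background cites earlier work in which CBT normalised prefrontal alpha. That motivates the hypothesis but is not a concurrent control.

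Three stronger readings should be resisted. A reader might infer that the EEG comparison as a whole, or the MADRS comparison, is uninterpretable. It is not, because the between-arm contrast is protected by randomisation. A reader might infer that the sponsor will run and report separate pre-post tests as confirmatory. The document does not say so. And a reader might quote the chance of a fall in at least one arm, 1 − (1 − p)², which is 45% / 75% / 94% at 0.2 / 0.3 / 0.4 SD. The hypothesis requires both arms, so that is the wrong event.

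**Conclusion.** The concern holds as a limit on what may be concluded. The article hypothesises, and its Discussion expects to demonstrate, that CBT with sham and CBT with active tDCS each reduce the asymmetry. The design identifies only the difference between them. This follows from the arms alone and needs no numerical assumption.

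The size is illustrative. If neither treatment did anything and time alone shifted the score by 0.1 to 0.4 SD of change, both arms would show a significant fall in about 1% to 56% of trials at 45 per arm. The shift and the tests are assumed. The outcome is secondary, and the between-arm comparison is sound. The remedy is nearly free and changes what the trial may claim, so it is worth making.

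**What to change.** 1. In Research Question, Aims, Hypothesis, make the between-arm difference in change of alpha asymmetry (active versus sham tDCS, both with CBT) the EEG hypothesis to be tested. State that within-arm changes are descriptive and will not be attributed to CBT or to the combination.
2. In the Discussion, replace the sentence "we also expect to demonstrate that these interventions are able to reduce the inter-hemispheric asymmetry of alpha EEG activity" with the between-arm statement.
3. In Statistical Analysis, Primary Outcome, state that the condition for the correlation analysis refers to the between-arm EEG result, or drop the condition.

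The cost is wording only: no new arm, patients, recordings or change to the primary analysis. The sponsor gives up a causal claim about CBT, and about the combination as a whole, on a secondary outcome.
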